## Abstract

**Background:**

Parkinson's disease (PD) is the second most common neurodegenerative disorder. As there is no definitive diagnostic test, its diagnosis is based on clinical criteria. Recently transcranial duplex scanning (TCD) of the substantia nigra in the brainstem has been proposed as an instrument to diagnose PD. We and others have found that TCD scanning of substantia nigra duplex is a relatively accurate diagnostic instrument in patients with parkinsonian symptoms. However, all studies on TCD so far have involved well-defined, later-stage PD patients, which will obviously lead to an overestimate of the diagnostic accuracy of TCD.

We have therefore set out to conduct a prospective study testing the diagnostic accuracy of TCD in patients with a parkinsonism of unclear origin.

**Methods/Design:**

We will enrol 250 consecutive patients, who are referred to neurology outpatient clinics of two teaching hospitals, for analysis of clinically unclear parkinsonism. Patients, whose parkinsonism is clearly diagnosable at the first visit, will be excluded from the study. All patients will undergo a TCD of the substantia nigra. As a surrogate gold standard we will use the consensus clinical diagnosis reached by two independent, blinded, movement disorder specialist neurologists after 2 years follow-up. At the time of TCD, patients will also undergo a SPECT scan of the brain.

**Discussion:**

As this prospective trial enrols only patients with an early-stage parkinsonism, it will yield data on the diagnostic accuracy of TCD that is relevant to daily clinical practice: The neurologist needs a diagnostic tool that provides additional information in patients with a clinically indefinable parkinsonian syndrome. The above described observational longitudinal study was designed to explicitly study this aspect in the diagnostic process.

**Trial registration:**

(ITRSCC) NCT00368199

## Background

Parkinson's disease (PD) is the second most common neurodegenerative disorder with a life-time risk of 2 percent in males and 1.3 percent in females [1]. Diagnosis is based on clinical criteria. In most cases the diagnosis of PD is straightforward when cardinal clinical signs and symptoms as bradykinesia, rigidity, and resting tremor are present [2]. However, these main features of PD are shared, at least in part, by atypical parkinsonian syndromes (APS), like multi system atrophy (MSA), progressive supranuclear palsy (PSP) and corticobasal degeneration), essential tremor (ET), vascular parkinsonism (VP), drug induced parkinsonism (DIP), dementia with Lewy bodies and Alzheimer's disease. Besides delineating PD from the above parkinsonian syndromes, distinguishing PD from normality can also be difficult, especially in early stage of the disease [3].

The gold standard for the diagnosis of PD is post-mortem neuropathological examination. Clinicopathological studies show that 2–25 % of the patients with IPD are classified incorrectly in the final stage of their disease, even by specialists in movement disorders, with MSA and PSP accounting for most false positives [2,4,5]. Diagnostic accuracy is certainly less than 90% in earlier disease, as Litvan et al. found that the median sensitivity for the diagnosis of PD increased from 73% at the first visit to 80% to the last visit after a mean follow-up of 9 years, and the median positive predictive value increased from 46 to 64% [6].

A reliable test to diagnose PD is important for two reasons. Prognosis and medical treatment in the various parkinsonian syndromes differ considerably and an objective disease marker would facilitate the development of neuroprotective therapies [7,8]. Several procedures have been proposed to diagnose PD: functional imaging with Positron Emission Tomography (PET)-scan or Single Photon Emission Computer Tomography (SPECT), olfactory- and neuropsychological tests, and DNA tests [9-12].

At the moment neuro-imaging techniques like PET and SPECT are the most widely used diagnostic tools [8]. PET is at least as reliable as SPECT, but its use in routine clinical practice is limited by high costs and a relative short half-life of its radioactive tracers [13-16]. Despite its widespread use, there is no consensus about the value of SPECT scintigraphy in the differential diagnosis of PD [8,17-19]. The ability of SPECT scanning to discriminate PD from normality and other parkinsonian syndromes varies greatly among different studies. A major issue here is that many studies use well-defined later-stage patients that are obviously not representative for the diagnostic problem that one wants to solve with a SPECT.

A more recent addition to the diagnostic armamentarium of the neurologist is transcranial duplex scanning (TCD) of the substantia nigra (SN) in the brainstem. In 1994 Becker discovered that patients with PD had bilateral hyperechogenicity of the SN [12], probably caused by iron deposition [20,21]. Several publications confirmed this observation that up to 90% of PD patients have increased echo-intensity of the SN. In healthy subjects and in patients with ET or VP this hyperintensity of the SN is only found in 10–25% [20,22-29].

This technique has high inter-observer reliability [22,25,29]. In a pilot study with 45 patients with PD or APS who underwent SPECT and TCD we found a positive predictive value of 95% of an abnormal TCD for an abnormal FP-CIT SPECT scan [30].

Based on this study we hypothesized that TCD of substantia nigra is a tool deserving a place in the diagnostic work-up of PD/Parkinsonism patients. TCD is less costly and less invasive than SPECT [31]. Since a diagnostic test for parkinsonian syndromes is especially valuable in the early stage of disease(s), we devised a prospective diagnostic study with a clinical follow-up after 2 years as surrogate gold standard. As SPECT is currently the most widely used diagnostic tool in parkinsonian syndromes we included this in the study to directly compare the two techniques as to their diagnostic capacities in this field.

## Methods/Design

### Design

Observational, prospective, longitudinal study.

### Setting

Consecutive patients will be recruited from the Neurology Outpatient Clinic of two hospitals: the University Hospital Maastricht in Maastricht and the Maasland Hospital in Sittard, The Netherlands. TCD will be done in the departments of Clinical Neurophysiology of the two above mentioned hospitals. SPECT scanning will be done in the departments of Nuclear Medicine of the two hospitals

### Ethical approval

The Institutional Review Board (IRB) of the University Hospital Maastricht has approved the study (MEC 05–228, 4 April 2006). (This IRB also functions as IRB for the Maasland Hospital in Sittard, The Netherlands). All patients will be asked for informed consent through a standardised information form that is also approved by the Institutional Review Board.

### Participants

250 consecutive patients with new parkinsonian signs and symptoms (of unclear origin at the time of visit) referred to the Neurology Outpatient Clinics of the University Hospital Maastricht (n = 150) and the Maasland Hospital Sittard, (n = 100).

#### Inclusion criteria

1. Patients with parkinsonian signs and symptoms of unclear origin at the time of visit at the Neurology Outpatient Clinic. In his/her differential diagnosis the treating neurologist should be considering one of the following conditions: PD, MSA, and PSP. ET, VP or DIP.

2. Age older than 18 years.

#### Exclusion criteria

1. Patients presenting with a clear unequivocal diagnosis of their parkinsonism.

2. Patients whose life expectancy is less than the required follow-up of two years.

### Methods

After informed consent all subjects will undergo a structured interview, neurological examination (See Additional file 1), TCD and SPECT within 6 weeks of the initial visit at the Outpatient Clinic. After two years all patients are re-examined by two movement disorder specialist neurologists for a final clinical diagnosis. This diagnosis serves as a surrogate gold standard to calculate the accuracy of SPECT and TCD to differentiate between PD and other types of parkinsonism.

### A. Interview and neurological examination

After informed consent the patient is seen on the outpatient clinic for the inclusion interview and neurological examination by a third party physician (i.e. a physician not treating the patient, and blinded for information in the routine clinical records). In the structured interview a standard form with the following items are discussed: medical history, used drugs and effect, intoxications, duration of complaints, and most affected body- side (See attachment 1). The following clinimetric scales are scored: UPDRS (parts I, III and IV) [32], Hoehn and Yahr score [33], Hamilton Rating Scale [34] for depression and the SCOPA cognition scale [35]. The Sniffin Sticks smell test is done according to a standardised protocol [36,37]. Finally, the including physician will try to reach a probable diagnosis, strictly applying the UK Parkinson's Disease Society Brain Bank criteria [2].

### B. SPECT

All subjects will undergo SPECT scanning within 6 weeks of inclusion in the study. In this study FP-CIT (^123^I-ioflupane, Nycomed, Amersham, U.K.) is used as presynaptic radiotracer. Medication (amphetamine, citalopram, fentanyl, cocaine, fluoxetine, fluvoxamine, paroxetine, sertraline, venlafaxine) which could interfere with the radiotracer is discontinued at least 5 half life times. After intravenous injection of the tracer, SPECT measures baseline dopamine transporter integrity in the brain. SPECT is performed with a triple head camera (MultiSPECT3, Siemens, Ohio, USA) equipped with high-resolution collimators. A semi-automatic template model programme is used to calculate the ratios between left striatal and right striatal and occipital regions respectively. Total time of acquisition is 30 minutes (45 seconds per frame for 40 views per detector). Zoom factor: 1.00 and the matrix size: 128 × 128. Filtered back-projection acquisition is performed. Images are filtered using a Butterworth filter with a cut-off value of: 0.4–0.5 and an order of 5. A division between the caudate nucleus and putamen is made. The ratios are corrected using Alderson's brain phantom, with known activities in the caudate nucleus and putamen. A binding of two standard deviations below healthy controls is considered as abnormal (FP-CIT 8.25 +-1.85 for putamen and 7.76 +-1.77 for caudate nucleus). Beside quantitative the scans will be also judged visually by the same nuclear specialist blinded for the final clinical diagnosis. If quantitative and visual judgments do not agree the conclusion of visual judgment is taken (unpublished data).

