### C. Transcranial Duplex Scanning (TCD)

TCD investigation is performed bilaterally through the pre-auricular bone window with a 2–4 MHz phased array transducer (SONOS 5500; Philips, Eindhoven, the Netherlands) by an experienced sonographer, blinded for the clinical data and SPECT results. The quality of the temporal bone window, the SN and Raphe nuclei (RN) of all subjects are scored directly by the sonographer blinded for the final clinical diagnosis and SPECT result. The quality of the bone window is scored as good, moderate or inconclusive.

Two different methods are applied for the evaluation of the echointensity of the SN. Firstly, the presence or absence of an obviously visible bilateral hyperechogenic SN is scored (qualitative method). The SN are scored as hyperechointens, not hyperechointens or inconclusive (= no typical configuration of hyperechointensity or low quality of the temporal bone window). Secondly, the area of an eventually hyperechogenic SN will be measured quantitatively (quantitative method). Both the right and left SN are measured from both sides, i.e. both temporal bone windows. After encircling, the area is automatically calculated. A hyperechogenic area of at least 0.2 cm^2 ^is classified as characteristic for PD. The RN are scored as: invisible (= iso-intense), just visible, visible (= hyper-intense) or inconclusive (= doubtful echointensity or low quality temporal bone window).

To determine inter-observer variability and to increase the power of the study a second sonographer will also judge the acquired echo data. A loop of 64 images of each patient will be acquired scanning the brainstem cranio-caudally and will be stored in order to allow for off-line analysis. Off-line the quality of the temporal bone window, SN and RN will scored by the second sonographer.

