### D. Regular Outpatient follow-up

The initial treating neurologist will remain responsible for the regular outpatient management of the patient included in the study. He or she will discuss the test results with the patient, and base his/her treatment plan on these. All further clinical decisions will be made by the treating neurologist.

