### Data analysis

Our main hypothesis is that TCD is as sensitive as SPECT to differentiate PD from other parkinsonian disorders. For the power analyses we assumed a sensitivity of SPECT of 90%, based on the analysis of our own data on 248 consecutive patients [19]. Assuming this 90% for TCD sensitivity we can accept as lowest border of the 95% confidence interval, 86% or higher:

*SD *= (√ (p1 (1-p1))/n → p1 = 0.9, sd 0.02, implying n = 190 patients, needed who have the hyperintensity of SN with TCD scanning.

In our pilot study 15% of the patients had an insufficient temporal bone window, so 224 patients are needed to compensate for the amount of inconclusive TCDs [28]. Based on this study we expect that 90% of all patients with inconclusive parkinsonism will ultimately have PD, so we set a target of initial 250 patients with unclear parkinsonism needed for this trial. We will calculate the sensitivity and specificity, positive predictive value, negative predictive value and diagnostic odd's ratio (OR) with its 95% confidence intervals (95% CI) of the first clinical judgment, TCD, FP-CIT SPECT scan and smell tests to predict the clinical diagnosis after 2 year follow-up. Accuracy is determined for all parkinsonian subgroups separately (PD versus APS, PD versus ET, and PD versus VP, PD versus DIP, and PD versus all other types of parkinsonism). For expected SPECT, TCD and smell tests scores for each parkinsonian disorder, see table 1.

**Table 1 T1:** Expected TCE, FP-CIT SPECT and odour recognition results for all parkinsonian disorders

Disease	FP-CIT SPECT abnormal, [19, 46]	abnormal SN TCD [47]	odour recognition deficit	cognition deficit
IPD	++	+++	+++	±
ET	Normal	normal	normal	normal
VP	normal *	normal	normal (?)	±
DIP **	normal (+)	normal (+)	normal (+)	normal (±)
MSA	++	±	+	±
PSP	++	± (?)	normal (±)	++

= normal FP-CIT tracer binding ratios

↓: FP-CIT binding of at least 2 sd. below healthy controls

* especially visual judgement together with CT or MRI

** At least 10% percent of the patients with DIP will develop to the PD [48]. So some patients in early stages of PD can theoretically present as DIP. Berg et al. investigated the relation between echointensity of SN on TCD and DIP after the start of antipsychotic drugs. Patients with serious parkinsonism scored higher echointensity as patients with mild or no parkinsonism [47].

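### The SPECT reader's only stated blinding is to a diagnosis made two years later, and that visual reading settles every SPECT result, so the TCD–SPECT comparison is at risk of review bias

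*Protocol article*

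**What the plan says.** Timing. Section B states: "All subjects will undergo SPECT scanning within 6 weeks of inclusion in the study". Under Methods, the reference diagnosis comes much later: "After two years all patients are re-examined by two movement disorder specialist neurologists for a final clinical diagnosis". Section D has the treating neurologist use the test results in between: "He or she will discuss the test results with the patient, and base his/her treatment plan on these".

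SPECT reading. Section B gives a quantitative rule, "A binding of two standard deviations below healthy controls is considered as abnormal", with control values for putamen and caudate nucleus. It then adds a visual reading: "Beside quantitative the scans will be also judged visually by the same nuclear specialist blinded for the final clinical diagnosis". Disagreements are settled as follows: "If quantitative and visual judgments do not agree the conclusion of visual judgment is taken (unpublished data".

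TCD reading. Section C has the scan made "by an experienced sonographer, blinded for the clinical data and SPECT results". A following sentence on scoring again shields the sonographer from SPECT, and also from the eventual diagnosis.

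Use of the results. Data analysis makes it the main hypothesis that TCD matches SPECT in sensitivity for PD. It also plans to estimate how well a PD-type TCD predicts an abnormal SPECT.

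**The concern.** Blinding a reader to something that does not yet exist removes no information from that reader. What could influence a visual reading at the time of the scan is what is already known: the signs and the most affected side, the first clinical judgment, and the TCD result. The blinding stated for the SPECT reader names none of these, although the article names the equivalent items for the sonographer.

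Two planned results are exposed:

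- **The TCD–SPECT comparison.** If the SPECT reader knows the clinical picture, SPECT is credited with information that TCD is denied. Baseline signs and the signs seen at two years are related, so a reading informed by the former will tend to agree with the final diagnosis.
- **The predictive value of TCD for an abnormal SPECT.** If the reader knows the TCD result, the two tests are no longer read independently, and agreement between them would tend to be overstated.

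Blinding matters more here because the outcome of the SPECT test is in the end a subjective judgment.

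**Working it through.** The plan gives no figure on this point, so there is none to reproduce. The check compares the relevant sections, works through the decision rule and then illustrates a possible size.

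**1. Timeline.** The scan is done by week 6 (section B). The final diagnosis is made at two years, about week 104 (Methods; section E). The gap is about 104 − 6 = 98 weeks. The date of the visual reading is not stated. Section D has results discussed with the patient and used for the treatment plan, so the reading presumably falls early in that gap. This is an inference.

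**2. Stated blinding of each assessor.**

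| Assessor | Clinical information | Other tests | Final diagnosis |
|---|---|---|---|
| Sonographer (C) | blinded | blinded to SPECT | blinded |
| Final assessors (E) | blinded to the treating neurologist's records | blinded to test results | they make it |
| SPECT visual reader (B) | not named | TCD not named | blinded |

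The SPECT reader is the only one of the three whose stated protection is confined to information from the future.

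**3. Decision rule.** Let V be the visual call and Q the quantitative call.

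| V | Q | Final SPECT result |
|---|---|---|
| abnormal | abnormal | abnormal = V |
| normal | normal | normal = V |
| abnormal | normal | abnormal = V |
| normal | abnormal | normal = V |

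The final result equals V in all four cases. The cut-offs, 8.25 − 2 × 1.85 = 4.55 for putamen and 7.76 − 2 × 1.77 = 4.22 for caudate nucleus, can be calculated but never change a result.

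**4. Possible size (assumptions, not in the document).** Let d be the share of PD patients in whom V and Q disagree, and f the share of those in whom outside information tips the visual call to abnormal. The shift in SPECT sensitivity is d × f.

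| d | f = 10% | f = 25% | f = 50% |
|---|---|---|---|
| 5% | 0.5 points | 1.25 points | 2.5 points |
| 10% | 1 point | 2.5 points | 5 points |
| 20% | 2 points | 5 points | 10 points |

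A second route starts from the plan's assumed SPECT sensitivity of 90% and treats it as a blinded value. Then 10% of PD scans are missed. If outside information turns 20–40% of these into abnormal readings, sensitivity rises by 10% × 20% = 2 to 10% × 40% = 4 points. On that premise the rise cannot exceed 100% − 90% = 10 points.

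The article gives neither d nor f, so these figures show a plausible range and do not estimate the bias.

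**The case against.** The strongest reply is that silence is not access. Nowhere does the article say that the SPECT reader sees TCD results or clinical data, and a fuller protocol may describe the reading procedure. Section C is itself loosely worded: one sentence blinds the sonographer to clinical data, while the next names the eventual diagnosis instead. The similar phrase in section B therefore cannot prove that its reader has baseline information. This stands, and it rules out the stronger reading that the comparator is unblinded and the comparison is biased. It does not remove the point. Both sentences in section C still name SPECT, whereas section B names neither TCD nor clinical data. The article also states a safeguard in section B, and as stated it does not work.

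Several further points limit the concern:

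- **Direction.** A flattered SPECT makes it harder to show that TCD is as sensitive, so for the main hypothesis the tendency is conservative. This stands for the clinical-information route. It does not cover the TCD-for-SPECT predictive value, which would be inflated.
- **Population.** Only unclear parkinsonism is enrolled, which limits how far baseline information could lead a reader to the right answer. This stands as a limit on size.
- **The 86% figure.** A reader might take 90% versus 86% as a tolerated gap between the tests and measure the bias against it. Data analysis gives 86% as the lowest acceptable confidence limit for TCD's own sensitivity. It is not a TCD–SPECT margin.
- **The Table 1 footnote.** The words "especially visual judgement together with CT or MRI" might be taken to show that the reader has other imaging. They annotate the expected result for vascular parkinsonism and are not a reading instruction, and the study procedures in the article schedule no CT or MRI.
- **The visual-priority rule.** It is prespecified, and TCD has a subjective score too. Giving priority to the visual reading is not an error in itself. Its effect is that the whole SPECT result depends on how well that reader is blinded.
- **The primary accuracy estimate.** TCD accuracy against the two-year diagnosis does not use the SPECT reading and is unaffected.

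**Conclusion.** The point holds as a risk of review bias, not as a demonstrated bias. The SPECT reader's stated blinding gives almost no protection when the scan is read, and it is narrower than the sonographer's. The result it should protect is in every patient a subjective call. The planned TCD–SPECT comparison and the predictive value of TCD for an abnormal SPECT are exposed. The estimate of TCD accuracy against the final diagnosis is not.

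The size cannot be computed from the article. Under the assumptions shown, SPECT sensitivity could shift by 0.5 to 10 points, and the tendency would favour SPECT over TCD. Confidence is high about what the text states and low about the amount of bias. The conclusion rests on one inference, that scans are read well before the two-year diagnosis, which section D supports but no section states. It is worth correcting because the main hypothesis is a comparison with SPECT and the correction costs very little.

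**What to change.** In section B, state that the nuclear specialist reads each scan blinded to baseline clinical data, the first clinical judgment and the TCD result, and records the reading before any results are released. This matches the protection that section C gives the sonographer.

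In Data analysis, prespecify a sensitivity analysis that repeats the TCD–SPECT comparison with the quantitative 2-SD result alone, using the cut-offs already in section B and a rule fixed in advance for combining regions and sides. The data are already being collected. Reporting how often the visual and quantitative readings disagree would also supply the rate that is now missing.

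The cost is one sentence on procedure and one extra table. The sample size does not change, since it is based on the precision of TCD sensitivity. The downside is that SPECT accuracy may look slightly lower than in routine reading, where clinical information is usually available.
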